# Psilocybin-assisted Existential, Attachment and RelationaL (PEARL) therapy for patients with advanced cancer: protocol for a multi-method feasibility trial

**DOI:** 10.1186/s40814-025-01706-5

**Published:** 2025-10-28

**Keywords:** Psilocybin, Psychotherapy, End-of-life, Depression, Palliative care, Attachment theory, Existential theory, Relational theory, Open-label, Pilot, Feasibility

## Abstract

**Background:**

Individuals with advanced cancer often experience high levels of distress for which there are few standardized treatment approaches. Our multidisciplinary team has combined existing evidence-based approaches into Psilocybin-assisted Existential, Attachment, and RelationaL (PEARL) therapy. PEARL therapy combines elements from psilocybin-assisted psychotherapy, including preparatory therapy sessions, a high-dose psilocybin session, and integration sessions, with important elements from evidence-based psychotherapies designed for patients with advanced cancer.

**Method:**

This open-label, single-arm clinical trial will assess the acceptability, feasibility, and safety of PEARL therapy among 15 patients with advanced cancer, using qualitative and quantitative methodologies. Participants will complete self-report questionnaires at four time points pre- and post-intervention, as well as a qualitative interview one month after PEARL completion. Feasibility will be evaluated in terms of recruitment, retention, and adherence rates, while safety will be assessed based on the number of participants experiencing no serious adverse events.

**Discussion:**

This study will yield important information about the acceptability and feasibility of PEARL therapy and contribute to growing research around the efficacy of psychedelic-assisted therapies. PEARL therapy has the potential to improve quality of life among those with advanced disease, and careful research is needed to guide public policy, legislation, therapist training, and clinical guidelines.

**Trial registration:**

NCT06416085; 2024–07-16.

**Supplementary Information:**

The online version contains supplementary material available at 10.1186/s40814-025-01706-5.

## Background

Advanced and life-threatening cancer brings multiple challenges, including progressive disability and physical burden of disease, complex treatment decisions, changes in social roles and relationships, and re-evaluation of sources of personal meaning and values. Additionally, the threat of mortality may evoke anticipatory fears related to the possibility of future dependency, isolation, physical suffering, dying, and death. The distress associated with advanced disease may be experienced as psychiatric symptoms of depression, anxiety, posttraumatic stress [1, 2], or as other forms of distress, such as demoralization, hopelessness, death anxiety, existential distress, spiritual suffering, the desire for hastened death, or loss of a sense of dignity [3]. The recent shift to earlier introduction of palliative care for those with advanced disease has been shown to improve quality of life and survival [4, 5], and yet, compared to management of physical symptoms, there remain relatively few standardized treatment approaches for psychological, social, and existential suffering [6].

A breadth of unique issues should be considered in the psychotherapeutic treatment of those with advanced or life-threatening disease. These include varying physical status, fluctuations in ability to engage in psychotherapy, practical and resource needs, relational changes imposed by the illness, needs of family and wider support systems, and differences in mortality salience and readiness to explore death-related concerns. A psychotherapeutic framework informed by existential, attachment, and relational theories may address this range of challenges while allowing for an individualized approach. An example of a psychotherapy informed by these theories is CALM (Managing Cancer And Living Meaningfully) therapy [7, 8], developed and researched previously by members of our team. CALM is a brief, semi-structured, manualized, individual psychotherapy for patients with advanced cancer and their loved ones. Within CALM, the general therapeutic strategy is to facilitate mentalization, which is the capacity to reflect on feeling states, to distinguish them from literal facts, and to accept the possibility of multiple perspectives on events in order to support “double awareness,” which is the ability to prepare for end of life while continuing to live in and enjoy the present [9, 10]. This approach has been shown to reduce psychological distress and improve end-of-life preparation in the advanced cancer population [11] and is a recommended standard for early psychological palliative care [12].

Preliminary research has demonstrated the potential of psilocybin-assisted psychotherapy in treating psychological distress experienced by patients with cancer [13, 14]. Psilocybin is a psychedelic compound that occurs naturally in the *Psilocybe* genus of mushrooms and exerts its primary effects via agonism at the serotonin 5-hydroxytryptamine type 2A (5-HT2A) receptor. At adequate doses, psilocybin induces profound alterations in thought, perception, and emotion, together with experiences of ego dissolution or mystical-type experiences [15]. Contemporary therapeutic use of psilocybin is usually paired with psychotherapy or a psychological support paradigm, whereby participants undergo one or a small number of guided, high-dose psilocybin treatment sessions preceded by preparatory sessions and followed by integration sessions [16]. Recent research has demonstrated, with large effect sizes, the benefits of psilocybin-assisted psychotherapy for reducing end-of-life distress in patients with advanced disease. Ross et al. [17] conducted a systematic review of clinical trials using psychedelic treatment in patients with serious or terminal illnesses and associated psychiatric issues. Ten studies with a total of 445 participants met the inclusion criteria. Combined data from the six open-label trials included suggested that psychedelic-assisted psychotherapy is associated with reduced cancer-related depression, anxiety, and fear of death. Furthermore, the four randomized controlled trials (RCTs), which predominantly used psilocybin, showed that psychedelic-assisted psychotherapy produced rapid and sustained improvements in cancer-related psychological and existential distress with large effect sizes [18–21]. Reiche et al. [22] conducted a similar systematic review, concluding that patients with life-threatening diseases, and associated depression and anxiety, can benefit from the antidepressant and anxiolytic properties of serotonergic hallucinogens, with some studies also reporting reduced fear of death and enhanced quality of life. These effects appear to be rapid and may be sustained for months to years following a single high-dose drug session [23–26].

A more recent systematic review [24] included an additional contemporary RCT exploring MDMA (3,4-methylenedioxymethamphetamine)-assisted psychotherapy for the treatment of anxiety and other psychological distress associated with life-threatening illness [27], along with a non-controlled trial of psilocybin-assisted therapy, delivered in a group setting, for the treatment of demoralization among long-term AIDS survivor men [28]; this review reached the same conclusions as Ross et al. [17] and Reiche et al. [22], while noting that most of the included studies lacked detailed information about the psychotherapeutic approaches employed, as well as other nonpharmacologic or contextual factors such as music playlists used [24]. Finally, two recent trials have demonstrated the feasibility, safety, and possible efficacy of psilocybin-assisted group therapy for patients with cancer [25, 26]. Beaussant et al. [29] conducted qualitative exit interviews among 28 participants in the Agarwal et al. [26] clinical trial and found that participants held positive attitudes toward the acceptability of group-based psilocybin-assisted therapy.

Combining psilocybin-assisted psychotherapy protocols [18, 20], with an existential, attachment, and relationally informed psychotherapeutic approach, we have developed a novel psilocybin-assisted psychotherapy intervention for patients with advanced cancer. This new intervention is called Psilocybin-assisted Existential, Attachment, and RelationaL (PEARL) therapy. The rationale for this feasibility trial is three-fold. Firstly, while it is well understood that the psychological effects of psilocybin are highly context-dependent [30], the psychotherapeutic components of existing psilocybin-assisted psychotherapy interventions have received little attention [24] and have not been informed by contemporary research regarding effective psychotherapeutic care of this population. Thus, defining potential therapeutic protocols, including the amount and type of psychotherapy, has been identified as a research priority [31, 32]. Second, patient preferences and expectancies may influence outcomes with psychedelics, and in most studies to date, patients have been motivated to engage, have self-referred, and in some cases have qualified for participation, despite having cancer in remission [18, 20]. It is unclear how feasible or acceptable PEARL might be for patients living with advanced cancer recruited within a comprehensive cancer center. Finally, the most relevant clinical outcomes remain unclear, with studies to date focusing on a variety of distress outcomes [31]. This protocol describes a feasibility and acceptability trial, the results of which will inform further intervention refinement and a randomized controlled trial (RCT) examining the efficacy of PEARL therapy.

### Objectives

1.a. To assess the feasibility of PEARL therapy with attention to recruitment, retention, and adherence.1.b. To assess the acceptability of PEARL therapy from the perspective of patients.1.c. To assess the safety of PEARL therapy.2.a. To explore the preliminary efficacy of PEARL regarding outcomes including death-related distress, depressive symptoms, anxiety, demoralization, spiritual wellbeing, quality of life, and desire for hastened death.2.b. To explore patient perspectives on the clinical relevance of these measurable outcomes.

## Methods

### Study design and setting

This is a single-center, open-label, one-arm, clinical trial using both qualitative and quantitative methodologies. Participants will be recruited from Princess Margaret Cancer Centre (PM), Canada’s largest comprehensive cancer treatment and research center, which includes a large Department of Supportive Care that provides outpatient psychosocial oncology and palliative care services.

### Participants

Participant inclusion criteria are as follows: (i) > 18 years of age, (ii) ability to speak and read English, (iii) no cognitive impairment, (iv) confirmed diagnosis of stage IV solid tumor/sarcoma/melanoma/lymphoma/endocrine cancer with expected survival of greater than 6 months, (v) at least mild depressive symptoms (PHQ-9 > 8), (vi) normal hepatic and renal function (INR < 1.5, AST/ALT < 2 × ULN, normal range bilirubin, PLT ≥ 150, eGFR > 45), and (vii) interest and ability to participate in the PEARL intervention as outlined. Furthermore, if sexually active and able to become pregnant, participants must be using effective birth control and cannot be pregnant or nursing for the duration of the study. Regarding medications and substances, for 1 week prior to the psilocybin session, participants must agree to refrain from (i) using any prescription medications not approved by the team and (ii) using any non-prescription medication, nutritional, or herbal supplement not approved by the team (exceptions include acetaminophen, non-steroidal anti-inflammatories, and common doses of vitamins and minerals). Additionally, participants must refrain from (i) taking any as needed medication on the morning of the psilocybin session (with the exception of daily and as needed opioid medication); (ii) using nicotine for at least 2 h prior to, and 7 h after, psilocybin administration; and (iii) using any psychoactive drugs, including alcohol, within 24 h of psilocybin administration.

Participant exclusion criteria include (i) cancer of, or metastasis to, the brain; (ii) symptoms consistent with delirium, psychosis, or other symptoms judged to be incompatible with establishment of rapport or safe exposure to psilocybin; (iii) history of past intolerability to psychedelics; (iv) past/present psychiatric diagnoses of bipolar disorder, psychotic disorder, active substance use disorder, or suicidality (as distinguished from desire for hastened death or readiness for death, per the discretion of the study team); (v) first degree relative with primary psychotic disorder if participant is under age 30; (vi) severe hypertension (SBP > 140 or DBP > 90) based on two readings on the same day; (vii) known paraneoplastic syndrome or “ectopic” hormone production by the primary tumor if incompatible with psilocybin, determined in consultation with the study palliative care physician; (viii) cardiovascular conditions including uncontrolled hypertension, angina, clinically significant ECG abnormality, transient ischemic attack in the last six months, stroke, peripheral or pulmonary vascular disease; (ix) uncontrolled epilepsy or history of seizures in the past 6 months; (x) gastrointestinal bleed in the past 6 months; (xi) participants with diabetes who are unable to skip a meal, require medication administration more than twice daily, or who have had symptomatic hypoglycemia within the prior 30 days; (xii) use of other investigational agents, psychoactive prescription medications (e.g., benzodiazepines, lithium, SSRIs), medications with primary pharmacological effect on 5-HT2A receptors (e.g., olanzapine), monoamine oxidase inhibitors, potent metabolic inducers (e.g., rifamycin, rifampin, rifabutin, rifapentine, carbamazepine, phenytoin, phenobarbital, nevirapine, efavirenz, paclitaxel, dexamethasone, St John’s wort), or inhibitors (e.g., HIV protease inhibitors, itraconazole, ketoconazole, erythromycin, clarithromycin, troleandomycin). In suitable patients, if safe to do so, contraindicated medications may be tapered prior to the start of the intervention.

### PEARL intervention

All participants will receive the PEARL therapy intervention, which consists of eight psychotherapy sessions delivered over a 7-week period. Each participant will be assigned a primary therapist for all sessions, and a secondary therapist will be present at the first psychotherapy session as well as the final preparatory, psilocybin, and first integration sessions. The PEARL foundations include existential, attachment, and relational theories, and the process is semi-structured, guided by the patient’s concerns, with a focus on joint creation of meaning between therapist(s) and patient, and facilitation of mentalization. PEARL therapists are PEARL-trained psychiatrists, psychologists, and spiritual care providers with expertise in treating patients with advanced cancer. Each therapy dyad will include at least one psychiatrist.

#### Initial psychotherapy sessions

Three initial sessions, 75 min in length, are aimed to develop a therapeutic alliance and explore the determinants of the patient’s distress considering four broad domains: (1) the physical experience (disease, symptoms, and management), (2) the relational context (changes in self-concept and relationships with close others), (3) spirituality and sources of meaning and purpose, and (4) their orientation to the future, hope, and mortality. A family caregiver will be invited to participate in one or more of these sessions to explore and support family functioning in the context of cancer and to prepare them for the psilocybin session, answer questions, and help them understand how to support the participant after the session.

#### Preparatory session

This 90-min session will be conducted 1 week before the psilocybin session within the treatment setting (a relaxed, calming space with controllable lighting and temperature, with availability of pre-selected recorded music via headphones and a surround sound speaker system) and will focus on preparation for the psilocybin session.

#### Psilocybin session

This session will last an average of 6–8 h. The patient will ingest a 25-mg psilocybin capsule administered by the study physician(s) within the treatment setting. Both therapists will act as supports or guides according to principles of psychedelic-assisted psychotherapy (the use of eye shades, music, inner-directed with therapists providing support as needed and facilitating a sense of safety) [33].

#### Integration session

This 90-min session occurring the day after the psilocybin session will support reflection on the experiences of and insights from the psilocybin session, understanding these in the context of the patient’s individual psychology, and considering their impact on the four content domains: (1) the physical experience (disease, symptoms, and management); (2) the relational context (changes in self-concept and relationships with close others); (3) spirituality and sources of meaning and purpose; and (4) their orientation to the future, hope, and mortality). Some attention will be paid to helping the participant continue their integration process on their own. A family caregiver will be invited to attend a portion of this session.

#### Follow-up sessions

Two further psychotherapy sessions, similar in nature and duration to the initial integration session, with the primary therapist will take place weekly to continue to explore and integrate the experience.

#### Investigational agent

Participants will ingest one 25-mg capsule of synthetic psilocybin at the beginning of the dosing session. Oral psilocybin, 25 mg capsules, are within the dosing range previously shown to be safe and well-tolerated in other clinical trials in this population [17, 18, 26, 29]. Psilocybin capsules are manufactured by Usona Institute under a collaborative agreement from their Investigational Drug and Material Supply Program.

#### Discontinuation criteria

Participants can withdraw from treatment or withdraw from the study at any time for any reason. The investigator may withdraw a participant if (a) the participant develops any conditions listed within the exclusion criteria (e.g., medical or psychiatric diagnosis/symptoms) that affect the safety of the participant, (b) the participant cannot comply with elements of the protocol that are critical for safety, or (c) in their clinical judgment, it is in the best interest of the participant. If the clinical team decides to terminate a participant from the study, they will explain to the participant, document the reason for removal, and ensure the participant has an appropriate follow-up support plan.

### Study procedures

The study schedule is organized as follows (see Fig. 1). Potentially eligible participants will be referred from outpatient clinics at PM. Research staff will contact potential participants to obtain consent for initial screening, which involves medical chart review, laboratory investigations, and psychiatric assessment. Participants assessed as potentially eligible will continue to the final screening procedures once informed consent for the main study is obtained. If participants meet all inclusion/exclusion criteria, they will be enrolled in the trial and complete baseline questionnaires (T0) within 1 week. Participants will begin the PEARL intervention within 1 to 2 weeks of T0. On the day following the psilocybin session, participants will complete questionnaires to assess the quality of the experience (T1). Participants will complete follow-up questionnaires 2 weeks (T2) following PEARL completion, a qualitative interview 1 month following PEARL completion (T3), and follow-up questionnaires 3 months following PEARL completion (T4). The assessments, intervention components, and questionnaires completed at each time point are outlined in the study calendar (Fig. 2).

**Fig. 1 Fig1:**
[figure not shown]
Study schedule

**Fig. 2 Fig2:**
[figure not shown]
Study calendar

### Sample size

We have chosen a target sample size of 15 participants. There is little consensus in the literature regarding sample sizes required for single-arm feasibility and acceptability studies, and guidance varies depending on study design and goals, as well as pragmatic issues such as the value of information, study cost, and other constraints [34]. In terms of human resources, time, and the price of psilocybin (a controlled substance that is expensive to purchase and import into Canada), this is a costly complex intervention to deliver, and therefore, the smallest meaningful sample size was preferred. The likely sample size of any future definitive RCT also informed our decision. While this is not a pilot RCT, it has been suggested that the size of a pilot trial should be informed by the size of the future definitive RCT with possible sample sizes of 10 to 75 depending on the potential effect size (from large to very small) [35]. Given the large effect sizes reported following previous psilocybin-assisted psychotherapy RCTs in this population (treatment arms in these trials ranged from 16 [20] to 29 [18]), a sample size of 15 for this single-arm study was deemed reasonable. Finally, our primary objectives include examination of both quantitative and qualitative indicators of feasibility and acceptability. Considering quantitative indicators, with a sample size of 15, we will be able to estimate, with 95% confidence, the anticipated recruitment rate of 40% with 25% absolute precision and the anticipated retention rate of 75% with 20% absolute precision. Considering qualitative indicators, samples of less than 20 have been deemed suitable for qualitative feasibility research [36].

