### Outcomes

#### Feasibility

Feasibility will be evaluated in terms of recruitment, retention, and adherence. Recruitment will be assessed by capturing the number of patients who consent to participate after referral and screening. Retention will be assessed by tracking completion of study measures across all time points. Adherence will be assessed by tracking the number of PEARL sessions completed.

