### Data analysis

#### Feasibility (Objective 1.a)

Based on guidance for conducting feasibility trials [38, 39], we have established clear progression criteria (green/proceed, amber/amend, red/stop), informed by previous research on similar interventions in similar populations, to determine if the study findings indicate that it would be feasible to examine the efficacy of PEARL therapy in a larger RCT. All progression criteria will be summarized using descriptive statistics.

*Recruitment* criteria are based on the percentage of interested and eligible patients who consent to participate. Green (progression to RCT) will be supported at or above 40%, amber (minor protocol amendment before progression) at 10–40%, and red (significant protocol amendment before progression) at or below 10%. We are aiming for consent rates as high as Griffiths et al. [18] documented in their psilocybin-assisted psychotherapy trial among cancer patients (41%). Given that the PEARL protocol is more demanding and time-consuming for patients, we will allow for a slightly lower consent rate.

*Retention* criteria are based on the percentage of participants completing primary endpoint (T3) measures. Green will be supported at or above 75%, amber at 40–75%, and red at or below 40%. Criteria are based on 18–26% loss to follow-up rates in similar studies [11, 17, 18], and we will allow for loss on the higher end given the time commitment and demands of the PEARL protocol.

*Adherence* criteria are based on the percentage of participants completing all eight PEARL intervention sessions. Green will be supported at or above 70%, amber at 40–70%, and red at or below 40%. Criteria are based on the CALM RCT at PM, which achieved 77.5% adherence (completion of at least 3 sessions) among a similar target population [11]. We have chosen a lower threshold given that we are planning more sessions within a shorter time frame.

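### The stated precision does not follow from the trial's own definitions: ±25 points for recruitment uses the wrong denominator, and ±20 points for retention is about 2 points too favourable

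*Protocol article*

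**What the plan says.** The Sample size section sets the target: "We have chosen a target sample size of 15 participants". The Abstract (Method) shows that these are the patients who are treated and studied, since the trial will "assess the acceptability, feasibility, and safety of PEARL therapy among 15 patients with advanced cancer".

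The Sample size section then gives a precision statement that covers two rates with one number of patients. It begins "with a sample size of 15, we will be able to estimate, with 95% confidence" and names "the anticipated recruitment rate of 40% with 25% absolute precision and the anticipated retention rate of 75% with 20% absolute precision". No formula or interval method is given.

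The two rates are defined elsewhere. Under Outcomes, Feasibility, recruitment is assessed by "capturing the number of patients who consent to participate after referral and screening". Under Data analysis, Feasibility (Objective 1.a), the recruitment "criteria are based on the percentage of interested and eligible patients who consent to participate". The same section defines retention as a percentage of participants who complete the T3 measures. It puts the green threshold at 40% for recruitment and 75% for retention, the same values as the anticipated rates.

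**The concern.** The two rates have different denominators. Retention is counted among participants, so 15 is correct there. Recruitment is counted among interested and eligible patients, of whom participants are the consenting part. One sentence nevertheless applies 15 to both. Even where 15 is correct, the stated half-width is smaller than the usual formula gives.

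Both rates feed the green/amber/red criteria for moving to a randomised trial. The precision statement tells the reader how firmly an observed rate can be placed on that scale. As written, it is somewhat too favourable for retention and considerably too pessimistic for recruitment. It also leaves unstated a planning number that the design implies: how many interested and eligible patients are needed to enrol 15.

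**Working it through.** **Inputs.** n = 15, 95% confidence, recruitment 40% ± 25 points and retention 75% ± 20 points (all from Sample size). The denominators are from Feasibility (Objective 1.a). I take the confidence level as two-sided, z = 1.96; the article does not state sidedness.

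**Formula.** Half-width d = 1.96 × √(p(1 − p)/n); inverse n = 1.96² × p(1 − p)/d².

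**1. Reproducing the stated figures with n = 15.**

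- Recruitment: 1.96 × √(0.40 × 0.60/15) = 0.248, or 24.8 points. This matches ±25. The inverse gives n = 3.8416 × 0.24/0.0625 = 14.75, rounded up to 15.
- Retention: 1.96 × √(0.75 × 0.25/15) = 0.219, or 21.9 points (about 53% to 97%). This does not match ±20. The inverse gives n = 3.8416 × 0.1875/0.04 = 18.01, so 18 to 19 participants.

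**2. Would another interval method give both figures?** Half-widths in points at n = 15:

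| Method | Recruitment 40% | Retention 75% |
|---|---|---|
| Normal approximation (Wald) | 24.8 | 21.9 |
| Wilson | 22.2 | 20.2 |
| Agresti-Coull | 22.3 | 20.7 |
| Jeffreys | 23.0 | 20.6 |
| Logit | 23.0 | 21.2 |
| Clopper-Pearson | 25.7 | 23.3 |
| Wald, continuity-corrected | 28.1 | 25.2 |
| Wald, t quantile | 27.1 | 24.0 |
| Wald, n − 1 | 25.7 | 22.7 |
| Wald, 90% interval | 20.8 | 18.4 |

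To the nearest point, no row gives 25 and 20 together. Wilson comes close for retention but gives 22 for recruitment, and its retention interval is asymmetric about 75% (49.7% to 90.1%).

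**3. Can 15 be the denominator of both rates?** If 15 were the interested and eligible patients, 40% consent would leave 0.40 × 15 = 6 participants. Retention precision would then be 1.96 × √(0.75 × 0.25/6) = 0.346, about ±35 points. So 15 cannot serve for both.

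**4. Recruitment with its own denominator.** Enrolling 15 at 40% implies 15/0.40 = 37.5, about 38 interested and eligible patients. The half-width is 1.96 × √(0.40 × 0.60/38) = 0.156, or 15.6 points (15.8 with 37). Wilson gives 14.9 and Clopper-Pearson 16.3 with 38. All are about ±16 or a little less, against the stated ±25.

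**The case against.** The best defence of the retention figure is rounding. Both precisions are multiples of 5 and no method is named. The Wald values 24.8 and 21.9, rounded to the nearest 5, give exactly 25 and 20; the Jeffreys and logit values do the same. This is plausible, and it shows how small the gap is. But the article does not say that it rounded so coarsely, the rounding goes in the favourable direction, and it does nothing for recruitment, where the denominator is wrong and the difference is about 9 points.

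The recruitment error is also conservative: the article claims less precision than the design would give, so no reader will over-trust the result. That stands. The replacement is conditional too. The article never states 38; it follows from 15 and 40%. If recruitment stops at 15 enrolled, the denominator depends on the observed consent rate, so ±16 is approximate. Study procedures puts final screening after consent to the main study, so those consenting may exceed 15. At the same rate, that would enlarge the denominator and move the figure further from ±25.

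Three stronger inferences are tempting but unsupported:

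- **That 15 loses its justification.** The Sample size section also cites cost, pilot sizes of 10 to 75 depending on effect size, treatment arms of 16 to 29 in earlier trials, and qualitative samples below 20. The precision sentence is one ground among several.
- **That the retention error causes the overlap with the amber zone.** The stated ±20 gives 55% to 95%, which overlaps amber (40–75%) almost as much as 53% to 97%. Any symmetric interval around 75% must overlap amber, because 75% is the green boundary.
- **That a progression decision changes.** The criteria are set on observed percentages and summarised descriptively; no interval enters the rule.

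**Conclusion.** The point holds as an error in stated figures. The recruitment half-width rests on the wrong denominator: about ±16 points is consistent with the article's definitions, not ±25. The retention half-width is 21.9 points, so ±20 is about 2 points too favourable. The recruitment error is the more substantive because it contradicts the article's own definition; the retention error alone could be loose rounding.

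The conclusion assumes two-sided 95% confidence, the normal approximation that reproduces the recruitment figure, and, for ±16, that 15 are enrolled at the anticipated 40%. The sentence should be corrected, but the error is not serious enough to hold up the trial.

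**What to change.** Keep 15 participants and restate the precision sentence, naming the method. By the normal approximation, retention of 75% is estimated to within about ±22 points among 15 participants. Recruitment of 40% is estimated to within about ±16 points, assuming that about 38 interested and eligible patients are approached to enrol 15. Add that the recruitment figure is approximate because its denominator depends on the observed consent rate.

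If exact intervals are added, label them Clopper-Pearson so that they are not read alongside ±22 as one method: 44.9% to 92.2% for 11 of 15, and 51.9% to 95.7% for 12 of 15. Neither count is exactly 75%.

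The cost is a short rewording. No patients are added, and no threshold or analysis changes. The retention figure becomes slightly less favourable and the recruitment figure more so.
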